## Abstract

**Background:**

Disordered gamblers have phenotypical and pathological similarities to those with substance use disorders (SUD), including exaggerated automatic cognitive processing of motivationally salient gambling cues in the environment (i.e., *attentional* and *approach bias*). Cognitive bias modification (CBM) is a family of computerised interventions that have proved effective in successfully re-training these automatic cognitive biases in SUD. CBM interventions can, in principle, be administered online, thus showing potential of being a low-cost, low-threshold addition to conventional treatments. This paper presents the design of a pilot randomised controlled trial exploring the effectiveness of two web-based CBM interventions targeting attentional and approach bias towards gambling cues in a sample of Dutch and Belgian problematic and pathological gamblers.

**Methods/design:**

Participants (N = 182) are community-recruited adults experiencing gambling problems, who have gambled at least twice in the past 6 months and are motivated to change their gambling behaviour. After a baseline assessment session, participants are randomly assigned to one of four experimental conditions (attentional or approach bias training, or the placebo version of the two trainings) and complete six sessions of training. At baseline and before each training session, participants receive automated personalised feedback on their gambling motives and reasons to quit or reduce gambling. The post-intervention, 1-month, and 3-month follow-up assessments will examine changes in gambling behaviour, with frequency and expenditure as primary outcomes, and depressive symptoms and gambling-related attentional and approach biases as secondary outcomes. Secondary analyses will explore possible moderators (interference control capacity and trait impulsivity) and mediators (change in cognitive bias) of training effects on the primary outcomes.

**Discussion:**

This study is the first to explore the effectiveness of an online CBM intervention for gambling problems. The results of this study can be extremely valuable for developing e-health interventions for gambling problems and further understanding the role of motivational implicit cognitive processes underlying problematic gambling behaviour.

**Trial registration:**

Netherlands Trial Register, NTR5096. Registered on 11 March 2015.

**Electronic supplementary material:**

The online version of this article (doi:10.1186/s13063-017-2190-2) contains supplementary material, which is available to authorized users.

## Background

Gambling disorder (GD) is a maladaptive pattern of wagering that persists in spite of detrimental consequences on major areas of life functioning, including impairment or loss of relationships, stress-related medical problems, elevated risk of suicide, criminal offences, and financial and vocational problems [1, 2]. The prevalence of lifetime GD ranges from 0.4% to 2% in the general population, with subclinical gamblers, also referred to as problem gamblers, contributing an additional 1.3–2.3% [3]. In addition, GD is comorbid with many mental health disorders, with the highest mean prevalence of substance use disorders (SUD), depression, and anxiety disorders [2–4].

Recent findings have shown that GD and SUD share many psychopathological features, including increased impulsivity and loss of control, impairments in response inhibition, cognitive flexibility and self-regulatory behaviour; craving, tolerance, and withdrawal symptomatology; gambling-related cue reactivity and selective attention; and neglect of other areas of life [5–10]. Similar to SUD, pathological gamblers show increased reward-seeking behaviour when anticipating winning together with lower reward and punishment sensitivity after winning or losing [11–15] (for a recent review of neuropsychological and neurobiological similarities between GD and SUD, see [16–18]). The clinical and neurobiological similarities between SUD and GD and their high co-occurrence further grounded the inclusion of GD within the substance-related and addictive disorders category in the latest *Diagnostic and Statistical Manual of Mental Disorders, Fifth Edition* [1].

The categorisation of GD as a form of behavioural addiction may also relate it to recent dual-process models of addictive behaviours, which postulate the existence of two intertwined but qualitatively different cognitive processes, i.e., impulsive and reflective processes, which underlie the onset and maintenance of addictive behaviours [19–22]. Impulsive processes involve fast automatic processing of motivationally salient substance-related cues in the environment driven by enhanced implicit motivation to consume the substance and decreased motivation to engage in other activities. Reflective processes are delayed, slower control processes of behaviour and emotion regulation, which involve goal-driven monitoring and decision-making processes, expectations and the evaluation of short-term and long-term consequences of behaviour. Through repetitive experiences with the substance, gradual classical conditioning learning processes, and habit formation, substance-related stimuli and behaviours can acquire incentive salience properties for triggering impulsive, automatic, and involuntary motivational states [17, 23]. As a result, environmental substance-related cues may be flagged as motivationally salient, grab selective attention, and endow the individual with a state of preparedness and behavioural approach tendencies towards cues that signal the upcoming reward [20]. If strong enough, these processes could interfere with or disrupt higher-order cognitive and affective mechanisms, which are necessary to enact cognitive and behavioural control and enable the individual to resist the temptation to exhibit addiction-related behaviours. Similar to SUD, one of the essential features of behavioural addictions is the failure to resist an impulse, drive, temptation, or craving for something that is potentially harmful to oneself or to others. The repetitive engagement in these behaviours ultimately “hijacks” individual resources at the expense of other personal life domains.

The hypersensitisation of impulsive processes and detriment of cognitive control and emotion regulation processes can put the individual more at risk of being stirred to gamble despite the occurrence of aversive consequences for the individual’s life and environment. These conditioned impulsive processes, named *cognitive biases*, include attentional processes (e.g., the automatic tendency to selectively attend and quickly process salient cues, also referred to as *attentional bias*) and automatically triggered action tendencies towards motivationally salient cues (e.g., the automatic tendency to approach gambling games and/or sites, also referred to as *approach bias*). A few studies have explored attentional biases in problematic and pathological gamblers (for a narrative review, see Hønsi et al. [24]). Both groups generally had faster reaction times when responding to gambling-related stimuli relative to other stimulus categories [8, 9, 25–27], consistent with results from studies with substance users [28]. Further, neuroimaging studies on cue reactivity in pathological and problematic gamblers compared to healthy controls identified increased responsiveness in fronto-striatal reward circuitry and brain areas related to attentional processing of gambling stimuli [6, 29, 30]. To date, no study has yet explored the occurrence of gambling-related approach tendencies.

Novel interventions have been designed to retrain these abnormal impulsive processes through the use of cognitive bias modification paradigms (CBM). CBM interventions, such as attentional bias modification (ABM) training [31] and approach bias modification training (AppBM) [32], aim to directly target the dominant cognitive biases playing a role in disorders. CBM interventions have often employed variations of the same computerised tasks used to assess the bias, with the addition of a contingency to manipulate the bias in the desired direction (for a review, see [21]). However, non-computerized varieties have also been developed [33]. Clinical studies with substance-dependent patients showed that the addition of AppBM and ABM interventions on top of standard treatment was effective not only in reversing the approach or attentional bias immediately after the training, but also in reducing relapse rates at 1-year follow up [34, 35] or in extending time to relapse in the experimental condition [36].

The maladaptive selective information processing and conditioned mechanisms underlying problematic and pathological gambling suggest that CBM paradigms may also be effective in reversing gambling-related cognitive biases, thus potentially reducing affective reactivity and changing habitual behaviours [13, 16, 24, 37]. To date there is no study exploring the effectiveness of CBM for GD. However, a first pilot study in another form of behavioural addiction, online gaming, reported that a single session of AppBM decreased gaming-related approach bias and positively affected gaming behaviour [38].

CBM interventions can in principle be administered online, thus showing potential of being a low-threshold, low-cost addition to more conventional treatments, such as cognitive behavioural therapy and motivational interviewing. This CBM feature is of particular value for new gambling treatment venues, since only 10% of problematic and pathological gamblers seem to seek help and enter treatment [39], likely because of shame and stigma about their condition or because they are unaware, reluctant, or unavailable to start face-to-face treatment [40, 41]. Providing web-based interventions can then increase the accessibility to help-resources for gamblers by ensuring anonymity and circumventing many of the barriers associated with traditional in-person treatments. However, there are indications that online CBM interventions may be less effective than clinical interventions [42], although a recent trial in smoking cessation provided promising results [43].

The present paper reports the full design of a pilot randomised controlled trial (RCT) exploring the potential effectiveness of ABM training and AppBM training delivered online. For efficiency reasons, the two training modules are tested under the same protocol, each one compared to its own control condition, which is analogous to running two studies simultaneously. In addition to the training programme, all participants receive personalised motivational feedback on their motives to gamble and reasons to reduce or quit gambling, in order to support their compliance wth the training intervention [44] and promote the intrinsic motivation to change their gambling behaviour [45].

### The present study: objectives and hypotheses

Being the first CBM study in the gambling field, the primary goals of the RCT are to explore (a) whether gambling behaviour decreases over time as a result of a CBM intervention, and (b) whether the two CBM interventions would successfully decrease or reverse the targeted bias. Primary outcomes are monthly frequency and expenditure (i.e., average amount of money spent per month) [46], assessed at baseline, after the intervention, and in the medium term (after 3 and 6 months). The secondary outcomes include measures of gambling-related attentional and approach bias, administered at baseline, after the intervention, and at the 3-month follow up. Participants’ severity of gambling problems and depressive symptoms are also monitored over all time points.

An additional secondary moderated mediation analysis will explore the moderating effects of trait impulsivity and interference control capacity (i.e., cognitive inhibition), which have been considered as endophenotypical vulnerability markers for SUD and GD [47, 48]. Greater impulsivity and diminished ability to cope with cognitive interference could lead to lesser ability to ignore gambling cues in the environment and to suppress prepotent behavioural responses, and could thus moderate the strength of the cognitive biases. In line with previous results of CBM studies in alcohol addiction [21, 35], any change in cognitive bias as a result of the training intervention would mediate changes in the gambling outcome variables. Further, participants with stronger cognitive biases and/or lower interference control capacity and higher impulsivity at baseline would benefit more from a CBM intervention than participants with weaker cognitive biases and/or stronger interference control capacity and lower impulsivity.

## Methods

### Study design

The study is a pilot, double-blind RCT with a four-group parallel design: two groups complete either the ABM training or the AppBM training and two control groups receive the placebo version of either training. The two placebo training varieties consist of a continuous assessment task without any stimulus-response contingency (i.e., participants are equally trained away from and towards both gambling and control stimuli [34, 35, 44]). The manipulation of the task stimulus-response contingency offers greater control over the comparison between experimental and placebo conditions, ruling out non-specific effects related to performing a computerised intervention, while retaining the same tasks, stimuli, and instructions. Given the absence of previous studies on the effects of CBM interventions with gamblers, the present design does not introduce a factorial combination of the two CBM interventions, since the two training interventions have never been individually tested with gamblers before, making it premature to experimentally test any interaction effect.

Participants complete a total of 10 sessions: a first baseline assessment session including the automated personalised feedback on their reported gambling motives and beliefs, six training sessions [49], a post-intervention assessment, and two follow-up assessment sessions after 3 and 6 months. Each training session starts with shortened automated personalised feedback about participants’ reported negative consequences of their gambling and advantages of reducing or quitting, after which motivation to train and craving for gambling are assessed, and proceeds with the training task (about 15 minutes). Participants can train almost daily, with a between-session interval of at least 20 hours; however, they are suggested to complete two to three sessions per week, allowing them to complete the full intervention in about 3 weeks. The total duration of the study is estimated to be about 7.5 months for each participant. The entire study, including all assessment measures, computerised tasks and automated personalised feedback, is delivered online through the LOTUS and JASMIN experiment delivery online platforms developed and managed by the University of Amsterdam.

The CONSORT participant flowchart [50] is presented in Fig. 1. The study protocol has been reviewed and granted ethics approval by the Medical Ethics Committee of the University of Antwerp (October 2014, Belgian registration number: B300201422158) and by the Ethics Committee of the University of Amsterdam (August 2014, Protocol number: 2014-DP-3774). Any major change in design and/or experimental procedure will be submitted to the ethics committees through amendments to the protocol. Any adjustment related to technical trouble-shooting and/or maintenance of the online platform does not require amendment with the ethics committees. The study has been registered in the Netherlands Clinical Trial Registry (identifier: NTR5096), listing all items of the World Health Organization Trial Registration Data Set (see also SPIRIT checklist in Additional file 1).

**Fig. 1 Fig1:**
[figure not shown]
CONSORT flow diagram of participants' progress through the phases of the RCT

### Participants and procedure

Participants are adults with gambling problems community-recruited in the Netherlands and Belgium through promotion advertisements and banners on local self-help websites for gambling problems and gambling online forums and organisations, and via flyers and promotion meetings around local addiction-care facilities. All study materials are both in Dutch/Flemish and French and participants can select their preferred language when creating their account. Participants are screened for eligibility at registration on the study platform according to the following criteria:Inclusion criteria: older than 18 years, having gambled at least twice in the past 6 months, seeking help for gambling problems (intrinsic motivation to treatment);Exclusion criteria: not being Dutch/Flemish or French native speaker, not having almost daily Internet access.

To encompass the full range of potential problems from problematic gambling to disordered gambling and to maximise participant inclusion, there is no inclusion criterion based on the severity of gambling problems (South Oak Gambling Scale score ≥ 3 [51]). Participants do not have any restriction in concomitant care and/or treatment while participating in the study, nor are they requested to provide information thereof. As an online self-help intervention, CBM training can be autonomously completed as an adjunct to any other type of intervention.

The use of broad eligibility criteria will ensure the inclusion of both problematic and pathological gamblers, thus not restricting the applicability of the interventions to severe gamblers only. This would also enhance the external validity of the study, since the results will be retrieved from a broad, subclinical and clinical sample of gamblers.

Upon registration, the goals, conditions, and procedure of the study are fully explained to participants, after which they provide their informed consent to participation. Participants regularly receive reminder emails about their open or upcoming training sessions and will be excluded from the study only if they do not complete the baseline assessment within 30 days after registration or if they request to be excluded. Data of excluded participants will not be included in the final analyses of the study outcomes. Participants’ data are permanently deleted from the database only upon participants’ explicit request to do so.

Once they complete the study, participants are free to enrol in a second booster training module. Participants assigned to the two placebo conditions are notified with their actual condition assignment and will randomly complete one of the two CBM programmes. Participants assigned to the active training conditions are notified of being part of the approximately 61% of participants who received one of the active interventions and will complete the training module they have not received during the experimental phase.

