#### Randomisation

Upon completing the baseline assessment session, participants are automatically randomised by the computerised system into one of the four experimental conditions in two steps: first, participants are randomised into three main experimental arms (ABM, AppBM, or placebo) with a 1:1:1.25 allocation ratio. Participants assigned to the placebo condition are then further randomised to receive the placebo version of either the AppBM or the ABM training, with a final allocation ratio equal to 1:1:0.62:0.62. Both randomisation steps are stratified by gender (i.e., participants are randomly allocated to one of the conditions to which the fewest participants of their gender have been assigned so far). The two-step randomisation procedure and the uneven ratio over the four experimental conditions were designed to increase the chance of receiving at least one active training intervention, while still allowing for a univocal comparison of each active training module with their respective placebo condition. Allocation concealment is fully ensured, since participant randomisation is fully automated and performed by a computer algorithm.

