### Data analysis

Multiple imputation of missing data will be performed for intention-to-treat analyses. Before running all analyses, all variable distributions will be screened for normality assumptions and univariate outliers. The use of parametric or non-parametric statistical tests will be adjusted accordingly. Each training group will be compared to its control group to check for any baseline difference in demographics (e.g., age and gender), severity of gambling problems (SOGS), and alcohol use. When significant differences are found and the relevant baseline variables also correlate with the outcomes of interest, they will be added as covariates in subsequent analyses.

Changes in gambling frequency and expenditure from baseline to the 6-month follow up will be examined through two separate 2 (condition: active training vs. placebo) × 4 (time: baseline, post-intervention, 3-month and 6-month follow up) mixed analysis of variance (ANOVA) analyses, one per training module. Each CBM condition is contrasted against its control condition, with the baseline assessment as reference time point for the following time points.

Changes in gambling cognitive biases as a result of each CBM intervention will be explored with a 3 (time: baseline, post-intervention, 3-month follow up) × 2 (condition: active vs. placebo training) × 2 (stimulus category: gambling vs. control) mixed ANOVA for approach bias (i.e., AAT task) and a 3 (time: baseline, post-intervention, 3-month follow up) × 2 (condition: active vs. placebo training) × 2 (trial type: on top vs. after) mixed ANOVA for attentional bias (i.e., VPT task). Any change in depression symptoms and gambling problems would be explored using two 2 (condition: active vs. placebo training) × 4 (time: baseline, post-intervention, 3-month and 6-month follow-up) mixed ANOVA analyses, one per training module.

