No multiplicity adjustment will be applied to correct for the multiple treatment arms since the two active training conditions are distinct treatments, compared to their own control condition. As mentioned earlier, in order to efficiently explore the main effects of both types of training modules, the design of the study involves running two clinical trials under the same protocol. Hence, the two trials can be considered as separate studies, making it unconventional to apply any adjustments to alpha levels. Furthermore, we emphasize that the study is strictly explorative in nature, so any significant findings should be received with some reservation until tested in further confirmatory RCTs, implying a lesser need for multiple-testing correction [67].

If significant effects of the CBM interventions on the cognitive bias and gambling outcomes are detected, a moderated mediation analysis for each CBM module will be carried out to explore the moderating effect of interference control capacity, impulsivity and baseline cognitive bias on the relation between CBM effects and the gambling outcome(s) [68]. Baseline cognitive biases, interference control capacity (Stroop task) and trait impulsivity (BIS-11) would be tested as moderators of the changes in cognitive bias resulting from training, which would further act as mediator of the change in the primary outcome(s).

Besides monitoring participant inclusion and drop-out, the analysis plan does not involve any interim analysis of collected data. The clinical trial will continue until the target sample size is reached unless participant attrition rate, defined as a drop-out at any moment after completing the baseline assessment, exceeds the expected 60% attrition rate of included participants [42]. The results of the study will be reported following the guidelines of the “Consolidated standards of reporting trials” (CONSORT) extension to non-pharmacological interventions [69].

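### The rule that drops the data of anyone who asks to be excluded has no time limit, so it reaches randomised participants and contradicts the planned intention-to-treat analysis

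*Protocol article*

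**What the plan says.** Four statements in the protocol article bear on this point.

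- **Who is excluded** (Participants and procedure). Participants are "excluded from the study only if they do not complete the baseline assessment within 30 days after registration or if they request to be excluded". The same sentence opens with the reminder emails for training sessions.
- **What happens to their data** (same section). The next sentence reads: "Data of excluded participants will not be included in the final analyses of the study outcomes". It does not separate exclusions before randomisation from those after it. Erasure is a further step: "data are permanently deleted from the database only upon" an explicit request from the participant.
- **When randomisation happens** (Randomisation). "Upon completing the baseline assessment session, participants are automatically randomised".
- **How outcomes are analysed** (Data analysis). "Multiple imputation of missing data will be performed for intention-to-treat analyses". The primary analyses are 2 × 4 mixed ANOVAs of condition by time, one set per training module.

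**The concern.** Intention-to-treat means that everyone randomised is analysed in the arm to which they were allocated. A rule that removes a randomised person, with all values already recorded, because that person asked to leave is not compatible with it. Imputation cannot repair the loss, because it works only on people who are in the analysis set.

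At stake is the definition of the primary analysis population. One analyst following Participants and procedure would drop these people; another following Data analysis would keep them. The choice would be made after data collection. Requests to leave can depend on how a participant is doing, for example on no perceived benefit or a relapse. If training affects gambling, that dependence can differ between an active arm and its placebo, and the groups compared would no longer be the randomised groups.

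**Working it through.** The plan has no figure of its own to reproduce here: it gives no number or rate of exclusion requests. The check is mainly a reading of the text, followed by a labelled illustration.

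**Step 1: place each exclusion route on the time line.**

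| Route | Timing relative to randomisation | Effect on the randomised set |
|---|---|---|
| Baseline not completed within 30 days of registration | Always before, since randomisation follows baseline | None |
| Participant asks to be excluded | Any time; no limit stated | Removes randomised people if the request comes after baseline |

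The request route cannot be read as confined to the pre-randomisation period. The sentence that contains it is also about reminders for training sessions, and training starts only after allocation.

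**Step 2: compare with the analysis statement.** Data analysis plans intention-to-treat with imputation. No section limits the exclusion rule or makes an exception to intention-to-treat for these people. The two statements therefore define different analysis sets.

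**Step 3: separate this route from attrition.** Data analysis defines attrition as follows: "defined as a drop-out at any moment after completing the baseline assessment", with 60% expected. Participants and procedure says that exclusion occurs *only* for the two reasons above. Someone who simply stops logging in has met neither, so silent drop-outs stay in the analysis set and their missing values go to imputation. The 60% is not the rate of this route.

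**Step 4: numbers of people.** With the target of 182 and first-step allocation 1:1:1.25 (placebo then split in two, 0.625 each):

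- active arm: 182 / 3.25 = 56
- placebo arm: 182 × 0.625 / 3.25 = 35

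An assumed 5 to 15% asking to be excluded would be 2.8 to 8.4 people in an active arm, or 1.75 to 5.25 in a placebo arm.

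**Step 5: illustrative shift.** If a fraction p of one arm is removed and their mean is g SD from that arm's full mean, the mean of those remaining moves by g × p / (1 − p). Neither p nor g comes from the article.

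| p (assumed) | g in SD (assumed) | Shift in arm mean |
|---|---|---|
| 0.05 | 0.3 | 0.3 × 0.05 / 0.95 = 0.016 SD |
| 0.10 | 0.5 | 0.5 × 0.10 / 0.90 = 0.056 SD |
| 0.15 | 0.8 | 0.8 × 0.15 / 0.85 = 0.141 SD |

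These values also assume no selective removal in the comparator arm. Similar selection in both arms would partly or wholly cancel.

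**Step 6: what keeping these people would recover.** Primary outcomes are recorded at baseline, post-intervention and the two follow-ups. Someone who leaves during the six training sessions has only a baseline value; keeping that person restores the randomised set, but later outcomes are imputed from other participants. Someone who leaves after the post-intervention assessment contributes observed outcomes that the present rule would discard.

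**The case against.** The case against making much of this has five parts.

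- **Attrition is not exclusion.** A reader might infer that, with 60% attrition expected, a large share of the sample would be removed. The article does not support that: only active requests trigger the rule, and their number may be very small. This objection stands.
- **Storage is not permission.** A reader might infer that the rule is needless because the data of people who leave normally stay in the database. But a request to be excluded may be a withdrawal of consent to analysis, short of asking for erasure. Which it is depends on consent wording that is not available here. This stands too, and the fix must be conditional on it.
- **Blinding.** Participants and investigators do not know the condition, and active and placebo versions share tasks, stimuli and instructions. This limits arm-related requests. It does not exclude them, because a participant can respond to training, or fail to, without knowing the arm.
- **The shift is not what the fix removes.** A reader might take 0.02 to 0.14 SD as bias that the change would eliminate. For people who leave before the post-intervention assessment, the unobserved outcomes stay unobserved, and imputation removes the bias only as far as the observed data predict them. This stands.
- **Exploratory pilot.** The article asks that significant findings be received with reservation. That lowers the stakes, but it does not settle which population is analysed.

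None of these reconciles the two statements. Nor is this detail that an article leaves to a fuller document: both the exclusion rule and the intention-to-treat plan are stated outright, and they conflict.

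**Conclusion.** The contradiction holds as written. The exclusion rule covers randomised participants who ask to leave and bars their data from the outcome analyses, while the analysis plan is intention-to-treat with imputation. This should be fixed.

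The consequence is of unknown and possibly small size. No request rate is given, the 60% attrition figure does not apply to this route, and blinding limits dependence on arm. The illustrated shift of 0.02 to 0.14 SD rests wholly on assumed values and on selection in one arm only. The rule permits arm-dependent selection; the article does not show that it will occur, or in which direction. The conclusion about the text is firm; the one about bias is only that it is possible.

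**What to change.** In Participants and procedure, confine the exclusion from outcome analyses to people who never completed baseline and so were never randomised. Then state that:

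- every randomised participant stays in the intention-to-treat set in the allocated arm, with data collected up to withdrawal used as far as the consent wording allows and later values handled by the planned multiple imputation;
- the only randomised participants omitted are those who request deletion or withdraw consent to use of their data, and their number is reported by arm.

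This recovers observed outcomes for people who leave after a post-baseline assessment. For earlier leavers it restores the randomised set through imputation and no more.

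The cost is about one sentence in the protocol, a check of the consent wording, and a count by arm in the participant flow. No new data are needed.
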